**Table 1. Study visits and procedures**

| Study procedure                                                                                                                                                                   | Enrolment/
randomisation | Follow-up
visits during
intervention | Household visit
(7 days after
treatment'
completion) | Pregnancy
follow-up | Delivery/
End of
pregnanc
y | One
month
after birth |
|-----------------------------------------------------------------------------------------------------------------------------------------------------------------------------------|-----------------------------|--------------------------------------------|---------------------------------------------------------------|------------------------|--------------------------------------|-----------------------------|
| Inclusion/exclusion criteria
check                                                                                                                                             | x                           |                                            |                                                               |                        |                                      |                             |
| Written informed consent                                                                                                                                                          | x                           |                                            |                                                               |                        |                                      |                             |
| ECG                                                                                                                                                                               | x                           |                                            | x                                                             |                        |                                      |                             |
| Demographics/medical history                                                                                                                                                      | x                           |                                            |                                                               | x                      |                                      |                             |
| Physical/clinical examination                                                                                                                                                     | x                           |                                            |                                                               | x                      |                                      |                             |
| Concomitant medication                                                                                                                                                            | x                           |                                            | x                                                             | x                      | x                                    |                             |
| Gestational age                                                                                                                                                                   | x                           |                                            | x                                                             | x                      | x                                    |                             |
| 
 
Nasopharyngeal and oropharyngeal swabs for maternal SARS-CoV-2 PCR
 
Venous blood (5 ml, IgG and IgM against SARS-CoV-2)
 
 | x                           |                                            | x                                                             |                        |                                      |                             |
| Maternal and perinatal outcome                                                                                                                                                    |                             |                                            |                                                               |                        | x                                    |                             |
| Umbilical cord blood (IgG and IgM against SARS-CoV-2)                                                                                                                             |                             |                                            |                                                               |                        | x                                    |                             |
| Placenta sample (histological examination)                                                                                                                                        |                             |                                            |                                                               |                        | X**                                  |                             |
| Neonatal nasopharyngeal aspirate***                                                                                                                                               |                             |                                            |                                                               |                        | x                                    |                             |
| Adverse events/Severe adverse events                                                                                                                                              |                             | x                                          | x                                                             | x                      |                                      |                             |
| Tolerability                                                                                                                                                                      |                             | x                                          | x                                                             |                        |                                      |                             |
| Signs and symptoms of COVID-19                                                                                                                                                    | x                           | x                                          | x                                                             | x                      |                                      |                             |
| Adherence to study medication                                                                                                                                                     |                             | x                                          | x                                                             |                        |                                      |                             |
| Ultrasound data                                                                                                                                                                   |                             |                                            |                                                               | x                      |                                      |                             |
| Infant health status check (telematics visit)                                                                                                                                     |                             |                                            |                                                               |                        |                                      | x                           |

\* In case of presence of fever and/or two symptoms suggestive of COVID-19 disease (fever, fatigue, cough (with or without sputum production), anorexia, malaise, muscle pain, sore throat, dyspnea, nasal congestion, or headache, diarrhoea, nausea and vomiting) in the previous 14 days, women will be collected a nasopharyngeal and oropharyngeal swabs for PCR analysis at any time.

\*\*In a sub-sample of participants (n=120).

\*\*\*12-24 hours of life.

#### **d. Laboratory procedures**

##### **Detection of SARS-CoV-2 infection**

A Real-Time polymerase chain reaction (PCR) Coronavirus (COVID-19) assay diagnostic test will be performed at the lab study hospital for specific detection of SARS-CoV-2 viral RNA. Real-Time PCR technology utilizes polymerase chain reaction for the amplification of specific target sequences and target specific probes for the detection of the amplified RNA. The probes are labelled with fluorescent reporter and quencher dyes.

##### *Principles of RT-PCR SARS-CoV-2 procedures*

The oligonucleotide primers and probes for detection of SARS-CoV-2 are selected from regions of the virus nucleocapsid (N) gene. The panel is designed for specific detection of the SARS-CoV-2 (two primer/probe sets). An additional primer/probe set to detect the human RNase P gene (RP) in control samples and clinical specimens is also included in the panel. RNA isolated and purified from upper and lower respiratory specimens is reverse transcribed to cDNA and subsequently amplified in the Applied Biosystems 7500 Fast Dx Real-Time PCR Instrument with SDS version 1.4 software. In the process, the probe anneals to a specific target sequence located between the forward and reverse primers. During the extension phase of the PCR cycle, the 5' nuclease activity of Taq polymerase degrades the probe, causing the reporter dye to separate from the quencher dye, generating a fluorescent signal. With each cycle, additional reporter dye molecules are cleaved from their respective probes, increasing the fluorescence intensity. Fluorescence intensity is monitored at each PCR cycle by Applied Biosystems 7500 Fast Dx Real-Time PCR System with SDS version 1.4 software (24–26).

##### *SARS-CoV-2 serological assays*

A multiplex high-performance immunoassay is being developed to quantify IgG and IgM antibodies that target fragments of the main SARS-CoV-2 protein interacting with the host, “spike” (S), through the Luminex technology already set in ISGlobal’s laboratory. Luminex platform allows analysing a wide range of immunological responses in front of other viral antigens (membrane (M), envelope (E) and nucleocapsid (N)) to increase the probabilities of serologically capturing the exposition and impact of the antigen diversity of the virus and its serological reactivity. Enzyme-linked immunosorbent assay (ELISA) or immunofluorescence assay (IFA) may also be used to detect IgG and IgM against SARS-CoV-2 in serum specimens of participants.

##### *Histological exam of the placenta*

A sub-sample of participants (n=120, randomly selected from the three study groups) will have a placental sample collected for histological analysis. The biopsies will be immediately placed in 25 mL of 10% neutral buffered formalin and kept at 4°C until processed and embedded in paraffin wax by standard techniques. Paraffin sections will be stained with hematoxylin and eosin, Giemsa’s stain and the periodic acid-Schiff technique. Placental histology will include the examination of inflammatory signs (such as presence of neutrophils and monocytes) in the subchorial space and the umbilical cord connective tissue (funisitis) and analysis of intervillous fibrin deposition (27).

#### **e. Safety**

The study is designed as a clinical trial in which pregnant women followed up prospectively from the antenatal care clinic contact until the end of pregnancy and their newborns for the first 24 hours of life.

Drug exposure to any drug during pregnancy may carry risks to both the mother and the developing foetus (28). Chloroquine and HCQ are on the WHO Essential Medicines List for use in rheumatic disorders, and is widely prescribed as an anti-inflammatory for rheumatoid arthritis (RA), systemic lupus erythematosus (SLE), and other autoimmune syndromes for more than 25 years including in pregnant women (18). Therefore, the safety of this treatment has been well established during pregnancy. In addition, there is wide evidence of the safety of CQ in the treatment and prevention of malaria in pregnancy in endemic areas (19). HCQ is associated with a better safety profile for daily and chronic use than CQ. Based on the limited *in vitro* data available, HCQ appears to be slightly more potent than CQ against SARS-CoV-2 (15).

With tens of millions of doses administered for malaria and autoimmune diseases, the side effect profile of HCQ is well described and the drug is generally well tolerated.

### HCQ side effects

With short-term administration (as opposed to chronic/years long use in rheumatologic disease management), the major AEs are gastrointestinal (nausea, vomiting, dyspepsia, abdominal cramps, and diarrhoea) and transient skin rashes. The gastrointestinal symptoms may vary by the specific generic manufacturer of HCQ, and are best managed by taking the drug with food or a glass of milk. A transient rash, most commonly morbilliform or psoriasiform, can develop in 10% of participants often with a sustained loading dose, and is often managed by lowering the dose. To avoid this potential side effect, this protocol is using a short loading dose, not a sustained one. Uncommonly, idiosyncratic leukopenia/ thrombocytopenia can occur and the drug should not be given to those with underlying bone marrow disorders. Lastly, hypoglycaemia can occur, and those taking insulin or glucose-lower drugs are at risk, and blood glucose should be monitored.

Manifestations of long term administration of HCQ, including retinitis, renal and hepatic disease, and cardiomyopathy are unlikely to occur in a short treatment duration such as the proposed 2-week exposure.

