#### *Inclusion criteria*

Women will be invited to participate in the trial and sign an informed consent if they meet the following inclusion criteria.

- Presenting with fever ( $\geq 37.5^{\circ}\text{C}$ ) and/or one mild symptom suggestive of COVID-19 disease (cough, dyspnoea, chills, odynophagia, diarrhoea, muscle pain, anosmia, taste disorder, headache) OR contact of a SARS-CoV-2 confirmed or suspected case in the past 14 days
- More than 12 weeks of gestation (dated by ultrasonography)
- Agreement to deliver in the study hospitals

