#### *Exclusion criteria*

- Known hypersensitivity to HCQ or other 4-aminoquinoline compounds
- History of retinopathy of any aetiology
- Concomitant use of digoxin, cyclosporine, cimetidine

- Known liver disease
- Clinical history of cardiac pathology including known long QT syndrome
- Unable to cooperate with the requirements of the study
- Participating in other intervention studies
- Delivery onset (characterized by painful uterine contractions and variable changes of the cervix, including some degree of effacement and slower progression of dilatation up to 5 cm for first and subsequent labours)

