##### **c) Electrocardiogram**

An electrocardiogram (ECG) will be performed using a mobile device (Kardia®). If the QTc is > than 500 milliseconds the woman will be considered as “study screening failure” and she will not be included in the study. If the QTc is < than 500 ms the recruitment procedures will continue.

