##### **d) Demographic, obstetric and medical data**

The woman's demographic and medical and obstetric data will be recorded onto a specific electronic case report form (eCRF). The physical examination of the woman at the ANC visit will be recorded and will include the following assessments: weight, height, gestational age by first trimester ultrasound assessment.

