#### **b) Treatment arm allocation**

Participants will be then randomized in a 1:1 ratio to HCQ (400 mg/day for three days, followed by 200 mg/day for 11 days) or placebo (2 tablets for three days, followed by one tablet for 11 days).

Allocation of participants to study arms will be done centrally by the trial's Sponsor (the Barcelona Institute for Global Health, ISGlobal) by block randomization. This method will ensure balanced allocation to both arms. The electronic CRF will assign automatically a study number to each participant, depending on her study group and recruitment site. Each number will be related to a treatment number, which assigns them to one of the study arms. Randomizations lists with treatment assignment for each study participant will be concealed in opaque sealed envelopes and only open in case of urgent need following study unblinding procedures.

A study card will be given to the participant in order to facilitate their clinical management in case they attend primary care centres or other hospitals.

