#### **Administration of study drugs**

Study tablets will be identically packaged in small opaque bottles. All study personnel, investigators and the participants will remain blinded throughout the trial.

Participants will receive a bottle containing 19 tablets of study medication. They will be instructed to take two tablets for first three days and one tablet for the following 11 days. The first day of treatment, drug administration will be supervised.

Women vomiting within the first 30 minutes of drug administration will be given a second full drug dose; women vomiting after 30-60 minutes of study tablets administration will be given an additional half dose of the drug.

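### The protocol says HCQ should not be given to women with underlying bone marrow disorders, but neither the exclusion criteria nor any other pre-randomisation rule carries this over.

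*Protocol*

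**What the plan says.** The section HCQ side effects, under 5.e Safety, describes what to expect from short-term use. It mentions uncommon idiosyncratic leukopenia and thrombocytopenia and adds that "the drug should not be given to those with underlying bone marrow disorders". The sentence has no qualifier for dose or duration.

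Eligibility is set out in section 5.a. The lead-in to the inclusion list reads "Women will be invited to participate in the trial and sign an informed consent if they meet the following inclusion criteria". The list then covers symptoms or contact with a case, gestational age, and agreement to deliver at a study hospital. The exclusion list opens with "Known hypersensitivity to HCQ or other 4-aminoquinoline compounds" and continues with retinopathy, three interacting drugs, liver disease, cardiac pathology including long QT, inability to cooperate, participation in other intervention studies, and onset of delivery.

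Section 5.c adds two further rules before allocation. Under Electrocardiogram, a QTc above 500 ms is a screening failure; below that, "than 500 ms the recruitment procedures will continue". Under Study groups, symptomatic PCR-negative women with no reported contact are withdrawn.

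Section 5.c also provides that the woman's "demographic and medical and obstetric data will be recorded onto a specific electronic case report form (eCRF"), and Table 1 has a row "Demographics/medical history" marked at enrolment. Under Treatment arm allocation, "Participants will be then randomized in a 1:1 ratio to HCQ" or placebo. Under Administration of study drugs, "All study personnel, investigators and the participants will remain blinded throughout the trial".

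**The concern.** The protocol names a group that should not receive the study drug but gives the sites no eligibility rule that keeps this group out. A coordinator who works through the written criteria would find a woman with a known marrow disorder eligible.

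The restriction can only work before allocation. Once she is randomised, site staff do not know which arm she is in, so they cannot withhold HCQ from her and still allow placebo. What is at stake is the safety of a small number of pregnant women who could be given a drug that the protocol says they should not have.

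**Working it through.** No figure in the plan bears on this point, so there is none to reproduce. The check compares the prohibition with each rule a woman must pass before she is randomised, and then asks whether anything later would catch the omission.

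**1. Rules before randomisation**

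| Place in the protocol | What it covers | Covers marrow disorders? |
|---|---|---|
| 5.a Inclusion criteria (3 items) | Symptoms or contact; gestation; place of delivery | No |
| 5.a Exclusion criteria (8 items) | Hypersensitivity; retinopathy; digoxin, cyclosporine or cimetidine; liver disease; cardiac pathology; cooperation; other trials; labour | No |
| 5.c Electrocardiogram | QTc above 500 ms | No |
| 5.c Study groups | PCR-negative, symptomatic, no contact | No |

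No item names haematological disease or captures it indirectly. No clause lets the investigator exclude a woman on general clinical judgement.

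**2. Comparison with the rest of the exclusion list**

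The same side-effects section regards retinitis, hepatic disease and cardiomyopathy as unlikely with a two-week course. Retinopathy, liver disease and cardiac pathology are nevertheless exclusions (the cardiac one also serves the QT concern). The marrow restriction is stated more directly than any of these and is absent from the list. The protocol gives no reason for leaving it out.

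**3. Steps after eligibility**

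- Baseline venous blood is for SARS-CoV-2 serology (5.c, SARS-CoV-2 testing), and Table 1 shows no blood count at any visit. Section 5.i mentions haemoglobin at the first antenatal visit, but only as a descriptive variable.
- Trial monitoring (5.h) verifies that participants meet the eligibility criteria. The According to protocol population (5.i) requires that all inclusion and exclusion criteria are met. Both rest on the list that omits the restriction, so neither would flag such a woman.

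**4. Order of events**

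Section 5.c describes medical history before group assignment and allocation. A known disorder could therefore be seen in time, but no rule tells the site to act on it.

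**5. Size**

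Inputs: 714 planned women (5.a, Trial design) and 1:1 allocation (5.c). The prevalence *p* of a known marrow disorder among otherwise eligible women is not in the protocol; the values below are assumptions.

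Expected women affected = 714 × *p*. Expected HCQ recipients = 714 × *p* ÷ 2.

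| Assumed *p* | Women affected | Of these, on HCQ |
|---|---|---|
| 0.01% | 714 × 0.0001 = 0.07 | 0.04 |
| 0.1% | 714 × 0.001 = 0.71 | 0.36 |
| 0.5% | 714 × 0.005 = 3.57 | 1.79 |

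These figures assume that no site applies the side-effects sentence on its own initiative, so for a given *p* they are upper values.

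**The case against.** The best reply is that the protocol already forbids this. The side-effects sentence is part of the protocol and is worded as an instruction. Section 5.g says that the study is directed by the protocol and its SOPs, which are to cover study visits and dispensing. A site that knowingly randomised such a woman would be going against a written sentence, and the medical history needed to recognise her is taken in time. The reaction is described as uncommon and treatment lasts 14 days. There are also daily phone calls about adverse events, provision to interrupt or stop the study drug, and a DSMB that can put the study on hold.

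Much of this stands. A reader might infer that the protocol has no safeguard at all, or that it affirmatively allows women with marrow disorders to be enrolled. The text supports neither reading: the prohibition is written down, and no passage says that these women may take part. The fault is that it was not carried into the rules that decide eligibility.

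The reply does not remove that fault. The sentence sits in background on side effects, no screening step refers to it, and five hospitals cannot be expected to apply it uniformly. Monitoring and the According to protocol definition both look to the criteria. The phone calls and stopping provisions act only after exposure, and with no scheduled blood count a fall in cell counts without symptoms could go unnoticed. The annexes are not at hand, but the text describes them as covering drug and dose rationale, contact, severity and consent, not eligibility.

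**Conclusion.** The point holds as a participant-safety inconsistency of low frequency. The protocol's own restriction on bone marrow disorders is missing from its eligibility criteria and from every other pre-randomisation rule, so following those rules as written admits a woman with a known disorder to 1:1 blinded allocation.

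The expected number is small: about 0.07 to 3.6 of 714 women, of whom 0.04 to 1.8 would be on HCQ. This rests entirely on an assumed prevalence of 0.01% to 0.5%. Only at the upper end is more than one woman expected to receive HCQ.

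A reader might go further and suspect harm to the trial's results. Nothing in the protocol supports that: no endpoint, analysis, power or sample-size figure depends on this criterion. It is still worth correcting, because the protocol contradicts itself on who may be dosed and the correction costs almost nothing.

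**What to change.** Add *Known bone marrow disorder* to the exclusion criteria in section 5.a, to be checked before randomisation against the medical history recorded at enrolment (section 5.c and Table 1). Because the criterion is limited to known disorders, it requires no blood count.

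The cost is one line in the protocol and in the eligibility check. No visit, laboratory test or data item is added. The downside is a very small loss of eligible women, about 0 to 4 of 714 over the assumed range, which does not call for a change in the recruitment target.
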